#### Qualitative data analysis

For the process evaluation interviews and focus groups, thematic analysis following the guidance of Miles & Huberman [30] will be conducted using NVivo qualitative analysis software. All interviews will be audio-recorded and transcribed verbatim. A researcher will remove all identifying information from the transcripts, including any references to patients, clinicians or local services.

An inductive approach will be used to provide new insights and a richer understanding of the data without using preconceived categories. Two members of the research team will first familiarise themselves with the transcripts. Open coding will be used (making notes and headings in the text to describe the content). Similar codes will be grouped under themes, and the identified themes and sub-themes will then be checked and refined. Inter-rater reliability in applying second level codes (or categories) will be calculated for 20% of the data.

#### Interim analyses {21b}

No interim data analysis is currently planned.

#### Methods for additional analyses (e.g. subgroup analyses) {20b}

Planned sensitivity and subgroup analyses will be outlined in the statistical analysis plan and signed off by the statistician and ISC prior to analysis.

#### Methods in analysis to handle protocol non-adherence and any statistical methods to handle missing data {20c}

Where data are missing for the primary outcome (MANSA at 6 months), individual level single imputations in which missing values are replaced by a fixed value following a predetermined rule will be used. The conditions in which imputation will occur will be specified in the statistical analysis plan, including circumstances where data would not be imputed (for example, the patient is deceased). Sensitivity analyses will be conducted to assess the impact of missing data under reasonable assumptions about the behaviour of those lost to follow-up. In each case, analysis will be carried out on the subset of participants for whom the outcome in question has been recorded and model estimates compared against analogous estimates from the imputation analysis to ascertain the impact of loss to follow-up in this study.

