### Sample size {14}

#### Quantitative sample size

In order to detect a medium effect size of 0.5, setting power at 90% for 5% significance, accounting for clustering based on an ICC of 0.002 (as observed within the DIALOG+ trial [15]), and applying a conservative design effect of 1.03, the total number of patients required in each country is 84 per group (*n* = 168 per country). After allowing for a drop-out rate of 20%, a total of 210 patients will need to be recruited to give the analysable sample of 168 or 84 per group. Therefore, 14 clinicians will need to be recruited in each country, with an average of 15 patients per clinician.

Clinicians of any background, including lay community workers will be eligible. Meetings held within each of the participating clinical services indicated that there were sufficient numbers of both clinicians and patients, with many outpatient clinics seeing 100+ patients with psychosis per day.

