#### Quantitative data analysis

The number of screened participants, eligible participants, and of those who refused participation or were not approached will be recorded. The analysis will assess the number of intervention sessions received by participants, and we will collect data on drop-out (including reasons for drop-out if available) from treatment. The intervention topics discussed in meetings will be tabulated.

Descriptive statistics will be reported for socio-demographic data for all participants. Nominal and ordinal data will be presented as proportions (frequency), whereas continuous variables will be described utilising central tendency and variability measures. The latter will be selected according to distributions found (parametric or non-parametric), which will be evaluated through normality tests and histograms (probability functions). To assess the effectiveness of DIALOG+, mean and standard deviations (or median and interquartile range) over the three time points (baseline, 6 months and 12 months) will be calculated, and analysis will test the significance of the differences between the means (or other parameters) of outcomes measured. The primary outcome analysis will be the comparison of mean MANSA scores between treatment groups at 6 months follow-up using a mixed-effects model. This model will account for clustering by clinician, baseline values of the outcome (MANSA) and site (Pakistan) as covariates. A full analysis plan will be developed prior to data analysis, which will consider which covariates should be adjusted for in the model and methods for dealing with missing data.

The analysis will be conducted on an intention-to-treat basis, and every effort will be made to collect complete data. Patterns of missing data will be explored, and a strategy for dealing with missing values will be developed in the formal statistical analysis plan. Methods for dealing with missing data will depend on the extent, type and distribution of missingness.

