Incremental cost effectiveness ratios (ICERs) will be calculated as the ratio of difference in costs over difference in outcomes.

Uncertainty will arise in the estimates of cost, QALYs and ICERs from two sources (1) sampling and (2) methodological assumptions. Methods similar to those for the RCT will be used in the economic evaluation to deal with missing data or censored data. Skewness and correlation in cost and outcomes data will be treated with Bayesian or frequentist techniques. For Pakistani results, ICERS will be adjusted for clustering effect at facility level. Probabilistic one-way or two-way sensitivity analysis will be carried out as a robustness check for the uncertainty surrounding the estimated ICERs due to assumptions used while estimating costs and outcomes.

A health economic analysis plan will be developed and agreed with the local research team and signed off by the International Steering Committee (ISC) prior to data analysis.

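### Missing 6-month MANSA scores are to be filled by single imputation of a fixed value; this conflicts with the open strategy stated elsewhere and, depending on the unnamed rule, biases the effect or understates its standard error

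*Protocol article*

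**What the plan says.** Two sections of the Protocol article deal with missing primary-outcome data.

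- **Item {20c}** (non-adherence and missing data) states that, where MANSA at 6 months is missing, "individual level single imputations in which missing values are replaced by a fixed value following a predetermined rule will be used". The SAP is to say when imputation applies and when it does not, with death as an example. Sensitivity analyses under reasonable assumptions about those lost to follow-up are promised. They include an analysis of participants with a recorded outcome, to be compared with the imputed analysis.
- **Quantitative data analysis** defines the primary analysis as a mixed-effects comparison of mean 6-month MANSA, with clinician clustering, baseline MANSA and site. It defers the missing-data strategy to the SAP: "Methods for dealing with missing data will depend on the extent, type and distribution of missingness".

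The Economic evaluation section adds: "Methods similar to those for the RCT will be used in the economic evaluation to deal with missing data or censored data". It refers to a separate health economic analysis plan.

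**The concern.** Item {20c} has already chosen a class of method for the primary outcome, while the quantitative analysis section says that the choice will follow from the pattern of missingness. Whoever writes the SAP cannot follow both.

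The class chosen is also a poor one for a primary analysis. A fixed value enters the model as if it had been observed, and nothing in the article carries the resulting uncertainty into the SE. If the value ignores the patient's arm, the filled patients contribute no treatment difference and the estimate is diluted. If it is derived from the patient's arm, the estimate survives but the filled values add apparent sample size and no residual spread, so the SE is too small.

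Outcomes are measured only at baseline, 6 and 12 months, so carrying the last value forward to 6 months means carrying baseline forward. Eligibility requires a MANSA score below 5, so some regression to the mean is likely in both arms, and a no-change value would then be systematically low. Any imbalance in drop-out would turn that into a difference between arms.

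At stake are the headline estimate, its confidence interval and its error rate.

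**Working it through.** **Inputs from Sample size {14}.** "In order to detect a medium effect size of 0.5"; "setting power at 90% for 5% significance"; "based on an ICC of 0.002"; "applying a conservative design effect of 1.03"; "the total number of patients required in each country is 84 per group". Drop-out is 20%, with 210 patients per country and 14 clinicians with 15 patients each. Allocation is 1:1.

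**Assumptions, not in the document.** Two-sided test; SD 1 (effects in SD units). In the simulation: correlation 0.5 between baseline and 6 months, and a mean improvement of 0.5 SD in controls.

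**The plan's own figure.** 168 / (1 − 0.20) = 210, as stated. So 210 × 0.20 = 42 patients per country are expected to be missing: 105 randomised and 84 observed per arm. The base size is 2 × (1.960 + 1.282)² / 0.5² = 84.06 per arm, which matches 84 before the design effect (84.06 × 1.03 = 86.6 after it). That gap is a separate matter. What counts here is that the trial is already sized for observed patients, so power does not depend on imputation.

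**By hand, 20% missing at random in each arm**

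1. True SE of the difference on observed data: √(2/84) = 0.154.
2. Arm-mean fill. Within-arm variance falls to 0.8 while n appears to be 105, so the model SE is √(0.8 × 2/105) = 0.123. The ratio is 0.123/0.154 = 0.80, an SE 20% too small. Type I error is 2 × [1 − Φ(1.96 × 0.80)] = 0.117, and coverage is about 0.88.
3. Common value, the same in both arms. The expected estimate is 0.8 × 0.5 = 0.40, with SE 0.8 × 0.154 = 0.123. Coverage of 0.5 is Φ(2.77) − Φ(−1.15) = 0.872.
4. Unequal drop-out with no true effect. The false difference is the difference in drop-out times the distance of the fill from the true mean. At 15% v 25%, baseline carried forward gives 0.10 × 0.5 = 0.05 SD. A poor score 2 SD below the baseline mean gives 0.10 × 2.5 = 0.25 SD.

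**By simulation.** 210 patients, 14 clusters of 15, ICC 0.002, 4000 runs per setting. The analysis was a baseline-adjusted linear model without a clinician or site term. Missingness was 20% per arm, either completely at random or dependent on baseline; each range spans these two mechanisms.

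| Handling of missing scores | Estimate (true 0.50) | Model SE / true SE | Coverage of 0.50 | Type I error (true 0) |
|---|---|---|---|---|
| Observed cases only | 0.50 | 0.99–1.00 | 0.95 | 0.06 |
| Baseline carried forward | 0.39–0.40 | 0.98 | 0.85–0.86 | 0.05 |
| Overall mean | 0.39–0.40 | 0.98–0.99 | 0.82–0.86 | 0.05 |
| Fixed poor score | 0.39–0.40 | 0.98–1.00 | 0.91–0.92 | 0.05 |
| Arm mean | 0.50 | 0.76–0.77 | 0.86–0.87 | 0.12–0.13 |
| Regression prediction | 0.50 | 0.76–0.77 | 0.87 | 0.12–0.13 |

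The fixed poor score also cuts power to 0.54–0.59, against about 0.955 for observed cases in the same simulation.

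With 15% v 25% drop-out in either direction and no true effect, baseline carried forward gives a false difference of 0.05 SD (type I error 0.075–0.084), and the fixed poor score gives 0.25 SD (0.29–0.30). These agree with step 4. The overall mean gives essentially none.

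**The case against.** The strongest reply is that little has been settled. The rule is unnamed, the SAP must be agreed before analysis with the statistician blinded until sign-off, and the quantitative analysis section leaves the method open. That stands as regards the rule, so no single magnitude can be attached to this trial. It does not remove the defect: item {20c} fixes the class of method, and every rule tried within that class failed in one way or the other.

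Further points that stand:

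- The observed-case analysis in item {20c} is close to what the primary analysis should be, and it could expose a discrepancy. As a sensitivity comparison, it would not correct the primary result.
- An arm-mean fill sits awkwardly with a predetermined, individual-level rule and with blinded analysts, so attenuation is the likelier failure.
- With a common value and equal drop-out, z is unchanged: 0.40/0.123 = 0.50/0.154 = 3.24. The effect is diluted, but there is no loss of power and no excess of false positives.
- The unequal splits have no source in the document.

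A reader might also infer more than the text supports:

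- *That one primary value in five will be invented.* 20% is a planning allowance. The SAP may exempt cases, and outcomes will be sought from all participants unless they refuse contact. One in five is an upper figure under the plan's own assumption.
- *That the ICER will rest on fixed values.* The rule in item {20c} covers MANSA at 6 months only. The economic wording could equally point to the open strategy, and it defers to a separate plan.
- *That the imputation ignores clinician clusters.* The rule is not stated, and the analysis model does account for clinician.

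**Conclusion.** The point holds. As written, item {20c} commits the primary MANSA analysis to single fixed-value imputation, and the quantitative analysis section conflicts with it. At up to 20% loss, the illustrative consequences are attenuation from 0.5 to about 0.4 SD with coverage of 0.82–0.87 (common value or baseline carried forward), or an SE 20–24% too small with type I error of about 12–13% (arm-mean or regression fill). Unequal drop-out can add a false difference: at 15% v 25%, none for an overall mean, 0.05 SD for baseline carried forward and 0.25 SD for an extreme poor score.

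These sizes rest on the assumed rules, SD scale, correlation, control improvement and drop-out patterns. The conclusion that one failure or the other occurs does not depend on any one of those values. The reference result for observed cases holds when missingness is completely random or depends on baseline. It does not show validity if drop-out depends on the unseen 6-month score.

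**What to change.** 1. In item {20c}, remove single fixed-value imputation as the primary approach. Make primary the mixed-effects model already planned (clinician clustering, baseline MANSA, site), fitted to all observed 6-month scores. Multiple imputation that respects clinician clusters is an acceptable alternative.
2. Keep sensitivity analyses for departures from missing at random. Fixed-value rules may stay there, with the rule and value named in the SAP before unblinding.
3. Align the section on quantitative data analysis, so that one primary method is stated and only the choice of sensitivity analyses depends on the observed pattern.
4. State in the Economic evaluation section that costs and EQ5D-5L data do not inherit single fixed-value imputation.

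No new data or larger sample is needed, since 168 observed patients per country is already the planned analysable number. The cost is wording, a little more programming, and reliance on missing at random given the model covariates. The data cannot verify that assumption, and the sensitivity analyses must probe it.

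### The missing-data sensitivity analysis promises to vary assumptions about patients lost to follow-up, but the only procedure stated compares complete cases with one fixed-value imputation

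*Protocol article*

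**What the plan says.** The protocol article covers missing primary-outcome data mainly in section {20c}, in three steps.

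- **Imputation.** For missing 6-month MANSA, "individual level single imputations in which missing values are replaced by a fixed value following a predetermined rule will be used". The rule, and the circumstances in which nothing is imputed (death is the example given), are left to the SAP.
- **Purpose of the sensitivity analyses.** "Sensitivity analyses will be conducted to assess the impact of missing data under reasonable assumptions about the behaviour of those lost to follow-up".
- **Procedure.** In each case, "analysis will be carried out on the subset of participants for whom the outcome in question has been recorded", with "model estimates compared against analogous estimates from the imputation analysis to ascertain the impact of loss to follow-up in this study".

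Two other sections bear on this. Under Quantitative data analysis, "The analysis will be conducted on an intention-to-treat basis", and the missing-data strategy is deferred to the SAP. Section {20b} adds that "Planned sensitivity and subgroup analyses will be outlined in the statistical analysis plan".

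**The concern.** The second and third steps do not fit together. The stated purpose is to make assumptions "under reasonable assumptions about the behaviour of those lost to follow-up" and see what follows. The stated procedure is an analysis that leaves those patients out, compared with one imputed analysis. A complete-case estimate has no term for the outcomes of the lost patients, so no assumption about them can be varied within it. If the words introducing the procedure mean each outcome, it is still a complete-case analysis.

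The comparison has limited use:

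- The complete-case mixed model is unbiased for the effect in all randomised patients only if missingness is ignorable given arm, baseline MANSA and site.
- The fixed-value imputation embodies one other assumption, set by whatever rule the SAP adopts.
- Agreement shows that these two assumptions give similar answers. It does not show what happens if those lost from one arm did worse.
- Disagreement may reflect only the imputation rule.

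The intention-to-treat statement makes unobserved patients part of the question. Participants are told their allocation (section {16c}), and the two arms ask different things of patients in the session. Outcome-related loss that differs by arm is therefore plausible, although nothing in the document shows that it will occur. The risk is a robustness statement resting on a comparison that cannot carry it.

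**Working it through.** **Inputs from the protocol article (Sample size {14} and Sequence generation {16a}).** Effect 0.5 SD; drop-out 20%; 168 analysable patients per country, 84 per group; 210 recruited per country; design effect 1.03; 1:1 allocation.

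**Inputs that are assumptions.** The split of missing patients between arms, and the shift d, in SD units, by which missing patients fall below observed patients in the same arm.

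**Step 1. Reproduce the planned loss.** 168 / (1 − 0.20) = 210, as stated. Expected missing: 210 − 168 = 42 per country, or 21 per arm if evenly split.

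**Step 2. Effect in all randomised patients.** With missing fractions m1 (intervention) and m0 (control), and shifts d1 and d0:

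all-randomised effect = observed effect − m1 × d1 + m0 × d0

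With an observed effect of 0.50, m1 = m0 = 0.20 and d0 = 0:

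| d1 (SD) | All-randomised effect | Complete-case estimate |
|---|---|---|
| 0 | 0.50 | 0.50 |
| 0.25 | 0.50 − 0.20 × 0.25 = 0.45 | 0.50 |
| 0.5 | 0.50 − 0.20 × 0.5 = 0.40 | 0.50 |
| 1.0 | 0.50 − 0.20 × 1.0 = 0.30 | 0.50 |

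An equal shift in both arms with equal loss cancels, and the effect stays at 0.50. With unequal loss it does not. At 30% missing in the intervention arm and 10% in control, a common shift d gives 0.50 − 0.20 × d, so 0.45, 0.40 and 0.30 for d = 0.25, 0.5 and 1.0.

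**Step 3. Tipping point.** Standard error per country = √(2 × 1.03 / 84) = 0.157. The smallest significant effect is 1.96 × 0.157 = 0.307. With m1 = 0.20 and d0 = 0:

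- significance is lost at d1 = (0.50 − 0.307) / 0.20 = about 0.97 SD;
- the effect reaches zero at d1 = 0.50 / 0.20 = 2.5 SD.

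This holds the standard error at its planning value. It ignores the gain from baseline adjustment and the added variance from multiple imputation.

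**Step 4. What the fixed-value comparator does.** If the rule gives the same mean imputed value in both arms, the imputed patients contribute no difference. With 20% missing per arm the estimate becomes 0.80 × 0.50 = 0.40. The gap of 0.10 from the complete-case result then comes from the rule. It matches the d1 = 0.5 row by coincidence and says nothing about other rows.

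**The case against.** The strongest reply has four parts.

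**The sentence has a second half.** It goes on to compare the complete-case result with the imputation analysis, which does include lost patients. The opening words could mean that, for each assumption tried in the imputation, complete cases serve as the reference. That reading is possible, and it is why the point is about wording. But section {20c} names only one imputation, by a fixed value, and no set of assumptions over which it would vary.

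**Details are deferred to the SAP.** This stands as a limit. The SAP may contain shift-based or reference-based analyses. It does not dispose of the point, because section {20c} states a population, a comparator and the conclusion to be drawn, and these do not meet the purpose it also states.

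**Fixed-value imputation can itself depart from missing at random.** That is correct. The planned comparison shows sensitivity to that one departure, though not to graded or arm-specific ones.

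**Loss may be small or harmless.** Section {18b} plans outcome collection for everyone who has not refused contact, with home visits, so stopping sessions is not the same as a missing outcome. Outcome assessors are blinded, and both arms have monthly sessions. Under the planning assumptions significance is lost only near a shift of 0.97 SD, which is large. All this lowers the likely impact, but 20% loss is still planned for.

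A reader might infer more: that the plan ignores lost patients altogether, that the imputed value is arbitrary, or that robustness will be claimed without support. The document supports none of these. Lost patients enter through imputation, the rule is predetermined but not shown, and no claim has yet been made. Nor should one say that the plan fails to test for missing-not-at-random loss. No analysis of observed data can test that; it can only explore the consequences of assumed departures.

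**Conclusion.** The point holds as a mismatch within section {20c}. The aim is to vary assumptions about those lost, while the stated procedure contrasts two fixed ones. Agreement between them would not establish robustness to the planned 20% loss. For intervention-arm shifts of 0.5 to 1.0 SD, the all-randomised effect would be 0.40 to 0.30 SD while the complete-case estimate remained at 0.50 SD. These figures rest on assumed shifts, 20% missing per arm, missing controls like those observed, and an observed effect equal to the design value. The tipping point of about 0.97 SD also rests on the per-country standard error at planning. It is worth correcting before analysis, with medium confidence, because the unseen SAP may already provide what is needed.

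**What to change.** Two changes.

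1. **Reword section {20c}.** Describe the complete-case analysis as a comparator that relies on missingness being ignorable given the model covariates. Do not present it as the means of judging the impact of loss.
2. **Specify a shift-based sensitivity analysis in the SAP, before unblinding.**
   - Include all randomised patients except those the SAP excludes from imputation, such as deaths.
   - Impute 6-month MANSA by multiple imputation under missing at random, respecting clustering by clinician and including arm, baseline MANSA and site.
   - Shift the imputed values separately by arm and refit the primary model at each combination.
   - Choose a range wide enough to reach the tipping point, for example 0 to −1.0 SD or beyond. A range stopping at −0.5 SD would fall short of the 0.97 SD in the working.
   - Report the tipping point and state whether a shift of that size is plausible.

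The cost is modest extra programming and the need to agree the shift range in advance. No new data are needed. If the SAP already contains such an analysis, only the wording of section {20c} needs aligning.
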